### Procedure for unblinding if needed {17b}

Unblinding is not required because this is an open-label study.

## Data collection and management

### Plans for assessment and collection of outcomes {18a}

Baseline data on all women invited to participate will be collected in a datasheet to control for unwanted bias in language, age, or other variables at enrolment. Data collection will be based on self-completed questionnaires in paper form (T0, T1, T2) and online (T3), together with data collected through information and management systems and data about app use. An English-translated version of the questionnaires is provided a Supplementary material to this study protocol. Additional data to confirm vaccination adherence and to monitor access to and outcomes of preventive health, health promotion, and care can be accessed through the regional health information systems.

### Plans to promote participant retention and complete follow-up {18b}

Women will be reminded to complete questionnaires via the app’s calendar function and via email and phone reminders.

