### Intervention description {11a}

Both groups of women (A and B) will be asked to complete an initial questionnaire to collect demographic and other data at time zero (T0). This paper questionnaire includes questions on health literacy, knowledge, and attitudes toward prevention and health promotion behaviours. At the same time, women in the experimental group will be assisted to download and instal the mHealth app on their smartphone or tablet.

During the study period, women in group A will be able to use the app, which was developed in collaboration with Area Science Park to support the first 1000 days of life, with all its features and content, while women in group B will be exposed to standard care. Specific content will be presented to the user according to the current pregnancy trimester or postpartum period following a scheduled routine; in any case, all content will always be available for free consultation throughout the usage period. Links to relevant institutional websites for further information will also be provided. The app will also include a FAQ (frequently asked question) section and a calendar function with the ability to set appointments and reminders. The app’s content and topics will include information on health preventive behaviours such as immunizations during pregnancy, weight gain during pregnancy, smoking abstinence and alcohol use, and adherence to routine childhood immunization schedules. The app will be an informative and educational tool aimed at improving health behaviours and well-being.

Three additional questionnaires will be collected from both groups of women during the study period at the end of the second and third trimesters (T1–2) and during the postpartum period (T3). While the second and third questionnaires will be distributed in printed form according to the women’s planned access to the Unit of Fetal Medicine and Prenatal Diagnosis, IRCCS "Burlo Garofolo", the fourth questionnaire will be made available online on the IRCCS "Burlo Garofolo" platform and in the app itself. Women will be reminded to complete it through the app’s calendar function and through email and phone reminders.

At the end of the trial period, women will also be asked to rate their appreciation of the app features and content by providing feedbacks in digital form and participating in focus group sessions.

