### Sample size {14}

Given that 55% of pregnant women living in Trieste received the DPT vaccine during pregnancy in 2018, and assuming that this rate increases to 70%, a sample size of 163 women per group (total of 326 women) with an alpha of 0.05 and a beta of 0.2 is required. Considering the possibility of spontaneous abortion and the possibility of losing participants during the follow-up period, the investigators determined to recruit 180 women per group (360 women in total).

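### Group A has an app reminder and an in-app T3 form that group B lacks, so T3 response, and with it the T3 comparisons, may differ by arm for reasons of follow-up alone

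*Protocol article*

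**What the plan says.** Under Intervention description {11a}, group A may use the app, while "women in group B will be exposed to standard care". T1 and T2 are printed forms handed to both groups at planned clinic visits. T3 is offered on the institute's online "platform and in the app itself".

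Reminders are described under {11a}, Strategies to improve adherence to interventions {11c}, Plans to promote participant retention {18b} and in the Discussion. Each place lists the same three channels: the app's "calendar function and via email and phone reminders", in the wording of {18b}. Email and phone are not limited to one arm.

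Outcomes {12} defines the primary outcome, DPT vaccination in pregnancy, from questionnaires evaluated at T3. Sections {20a} and {20c} restrict the main analysis to randomized women whose main outcome is available. Section {20c} adds that reasons for dropout will be detailed and that a sensitivity analysis will explore missing data. Vaccination in pregnancy is also collected with support from the regional health information systems ({11a}); Participant timeline {13} and {18a} describe those records as a means of confirmation.

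**The concern.** The two arms are not followed up in the same way at the time point that supplies the primary outcome. One arm gets an extra prompt and an extra way to answer, and both come through the intervention itself. Nothing in the article acknowledges or offsets this.

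Because the main analysis is of women with an available outcome, response decides who is counted. An app-based channel works through app users, and app use may be related to vaccination, smoking, breastfeeding or health literacy. Response could then depend on the outcome more in one arm than in the other, and randomization no longer protects the comparison among responders. The Discussion calls loss to follow-up probably the greatest risk to the study and lists the app calendar among the remedies, yet that remedy can reach only one arm.

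**Working it through.** **Inputs from the protocol.** Control rate: "Given that 55% of pregnant women living in Trieste received the DPT vaccine during pregnancy in 2018". Target: "assuming that this rate increases to 70"%. Error rates: "with an alpha of 0.05 and a beta of 0.2 is required". Result: "a sample size of 163 women per group (total of 326 women"), raised so that "the investigators determined to recruit 180 women per group (360 women in total").

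**The plan's own figure.** With a two-sided test (sidedness is not stated) and pooled variance under the null:

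n = [1.960·√(2·0.625·0.375) + 0.842·√(0.55·0.45 + 0.70·0.30)]² / 0.15² = 162.3, rounded up to 163.

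The stated figure is reproduced. The step to 180 allows for a loss of 1 − 163/180 = 9.4%, the same in both arms. The sample size is sound and is not the problem here.

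**Where the arms differ in follow-up.**

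| | Group A | Group B |
|---|---|---|
| T1, T2 form | paper, at clinic visit | paper, at clinic visit |
| T3 form | institute platform, or app | institute platform |
| Reminders | email, phone, app calendar | email, phone |

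**When this biases the result.** Let p be the true vaccination rate, and r_v and r_u the T3 return among vaccinated and unvaccinated women. The rate among responders is

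observed = p·r_v / (p·r_v + (1 − p)·r_u).

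With the same p in both arms, the observed rates agree whenever the ratio r_v/r_u is the same in both arms. Unequal response alone therefore creates no bias under no effect.

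**Illustrations.** The true rate is 55% in both arms, with 180 randomized per arm. All return rates are assumptions, since the protocol gives none. The last column is the approximate chance that a two-sided 5% test rejects, with the normal approximation and the expected numbers of responders.

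| Return in A (vacc./unvacc.) | Return in B (vacc./unvacc.) | Observed A | Observed B | Difference | Rejects |
|---|---|---|---|---|---|
| 95/95 | 80/80 | 55.0% | 55.0% | 0 | 5% |
| 95/85 | 95/85 | 57.7% | 57.7% | 0 | 5% |
| 95/85.5 | 80/72 | 57.6% | 57.6% | 0 | 5% |
| 95/85 | 85/85 | 57.7% | 55.0% | +2.7 | 7.8% |
| 95/80 | 85/85 | 59.2% | 55.0% | +4.2 | 11.6% |
| 95/90 | 90/80 | 56.3% | 57.9% | -1.6 | 5.9% |
| 95/95 | 85/75 | 55.0% | 58.1% | -3.1 | 8.5% |
| 95/95 | 90/70 | 55.0% | 61.1% | -6.1 | 19.5% |

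Worked examples:
- +2.7: 0.55·0.95 / (0.55·0.95 + 0.45·0.85) = 0.5225/0.9050 = 0.577.
- +4.2: 0.5225 / (0.5225 + 0.45·0.80) = 0.5225/0.8825 = 0.592.
- -6.1: group B shows 0.55·0.90 / (0.55·0.90 + 0.45·0.70) = 0.495/0.810 = 0.611, against 0.550 in A.

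Relative to the 15 points planned for, +4.2 is 28% and -6.1 is 41%. The -6.1 case works against the app: with a true 70% in A and flat return there, the observed difference would be 70.0 − 61.1 = 8.9 points instead of 15.

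**The case against.** The best defence is that the asymmetry is small. Email and phone reminders and the online platform are described without restriction to one arm, so most of a symmetric follow-up is already in place and the app only adds to it. T1 and T2 are completed on paper at clinic visits; knowledge, behaviours and health literacy are measured there as well as at T3. Vaccination has a second source in the regional records, Data management {19} merges those records into the final data set, and a missing-data sensitivity analysis is planned.

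The illustrations can also be challenged. The +4.2 case needs unvaccinated women in A to return T3 less often than those in B (80% against 85%), which an added reminder does not explain; holding them at 85% gives +2.7. The -6.1 case has the app group's advantage falling mainly on unvaccinated women, which fits poorly with an app that reaches the more health-minded.

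Much of this stands. A reader might infer that follow-up runs only through the app, that every questionnaire outcome is affected, or that bias is certain. The documents support none of these: other channels exist, T1 and T2 have no in-app form, and bias needs a response–outcome link that differs by arm. Nor do they say that only women who open the app are prompted.

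What remains is that group A's extra channel and route are written into the plan, at the time point that yields the primary outcome, with analysis limited to available outcomes. The regional records are described as confirming vaccination while {12} still names questionnaires as the source, and no record-based measure is described for health literacy, knowledge, smoking or alcohol. A sensitivity analysis examines missing data afterwards; it does not remove an avoidable cause of it.

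**Conclusion.** The point holds as a risk built into the stated follow-up, concentrated at T3. T3 response may differ by arm, and if its dependence on the outcome also differs by arm, the T3 comparisons may be biased. Neither size nor direction can be read from the protocol. On vaccination, with no true effect, the assumed return rates give roughly +3 to +4 points or -6 points, and several plausible patterns give none. These figures show what could happen and are not estimates. At T1 and T2 only the app reminder could differ, so exposure there is much smaller. This does not invalidate the design, but it is worth correcting because it is avoidable and the Trial status section says recruitment has not begun.

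**What to change.** 1. Use the same email and phone reminder schedule in both arms, and the same web link to the institute platform for T3.
2. Remove study-questionnaire reminders and the T3 form from the app. Its calendar can stay for health content and appointments.
3. Report questionnaire response by arm at T1, T2 and T3.
4. For the primary outcome, take vaccination status from the regional records for all randomized women, so that it does not depend on T3 response. The protocol already plans to collect these data. This assumes that the records capture vaccination equally completely in both arms, which the article does not address and which should be checked.

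The cost is a wording change in {11a}, {11c}, {12}, {18b} and the Discussion, plus disabled app functions. Group A loses one redundant reminder channel, which an extra email or call in both arms could replace. The sample size is unaffected.

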### Data management {19}

Data entry for the printed questionnaires will be possible through a digital interface similar to that used for data collection during follow-up via the online survey. Each participant is linked to a unique participant code; duplicates will be checked after data entry. Data will be then merged with other sources, the utilization data, and the health information system to obtain the final complete data set.

### Confidentiality {27}

All participants are assigned a specific ID code that will be used throughout the study to track all relevant information and questionnaires to ensure pseudo-anonymization.

### Plans for collection, laboratory evaluation, and storage of biological specimens for genetic or molecular analysis in this trial/future use {33}

See the section ‘Additional consent provisions for collection and use of participant data and biological specimens {26b}’, no biological samples will be collected.

## Statistical methods

### Statistical methods for primary and secondary outcomes {20a}

Categorical variables will be presented as absolute numbers and percentages; continuous variables will be presented as mean and standard deviation or median and interquartile range, depending on data distribution assessed visually and using the Kolmogorov–Smirnov test.

The main population characteristics of the participating women in both groups (age, marital status, living area, country of origin, socioeconomic level, educational and occupational level, etc.) will be compared to assess the effectiveness of randomization. Differences between the two groups on categorical outcomes will be assessed using the chi-square test or Fisher’s exact test, as appropriate. Comparisons between continuous variables will be made with nonparametric Student *T* or Mann–Whitney tests, as appropriate for the data distribution. The main analysis will be an ‘intention-to-treat design’: all randomized women with an available main outcome will be assigned to the associated group regardless of intervention. A per-protocol analysis will also be performed. A statistically significant difference will be considered to exist if the *p*-value is < 0.05.

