### Participant timeline {13}

Pregnant women will participate in the study from the first antenatal echography until the end of the first 1000 days of their child’s life. The evaluation time points are enrolment in the study (T0), end of the second trimester (T1), end of the third trimester (T2), and the postpartum period (T3). Data on app use will be collected throughout the study period. Other variables collected (T0) include data describing the population and potential confounders (e.g. age, country of origin, marital status and composition, socioeconomic level, educational level) and risk/protective factors (e.g. smoking and alcohol habits before pregnancy, data on current pregnancy).

Data collection will be based on self-completed questionnaires in paper form (T0, T1, T2) and online (T3), as well as data collected using information and management systems, and data on app use.

The questionnaires are provided as a Supplementary Material to this study protocol. Additional data to confirm vaccination adherence and to monitor access to and outcomes of preventive health, health promotion, and care can be accessed through the regional health information systems.

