### Methods for additional analyses (e.g. subgroup analyses) {20b}

No additional analysis is planned.

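### T0 measurements enter no stated outcome analysis: unadjusted two-group tests give up some precision, modest for DPT uptake and larger for repeated scores

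*Protocol article*

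**What the plan says.** The section on statistical methods for primary and secondary outcomes {20a} assigns chi-square or Fisher's exact tests to categorical outcomes. These include the primary outcome, DPT vaccination in pregnancy. For continuous variables it says "Comparisons between continuous variables will be made with nonparametric Student" T or Mann–Whitney tests. (Calling Student's t nonparametric is a separate wording slip.) No model with covariates is named for any outcome.

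The baseline data are there to be used. Of the T0 form, Intervention description {11a} says "This paper questionnaire includes questions on health literacy, knowledge, and attitudes toward prevention and health promotion behaviours". Participant timeline {13} adds "Other variables collected (T0) include data describing the population and potential confounders", with age, country of origin, socioeconomic level and educational level among the examples. In {20a} the stated use of baseline characteristics is a comparison of the groups to judge whether randomisation worked. The section on additional analyses {20b} states "No additional analysis is planned".

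Sequence generation {16a} randomises enrolment days, so all women enrolled on one day share an arm. Outcomes {12} lists health literacy (HLS-EU-Q16) at T1, T2 and T3.

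**The concern.** A T0 measurement that predicts the outcome can remove part of the outcome's variance from the group comparison. A two-group test at follow-up ignores that information, so the interval is wider than the collected data allow.

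Comparing groups at baseline may reveal an imbalance but corrects nothing. If age, education or attitude to vaccination differs between arms by chance, the planned tests carry that difference into the result. Choosing adjustment only after seeing an imbalance would invite selective reporting, so the choice belongs in the plan. Randomising days rather than women makes such imbalance somewhat more likely if women seen on the same day resemble one another.

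**Working it through.** **Inputs from the protocol (Sample size {14}).** "55% of pregnant women living in Trieste received the DPT vaccine during pregnancy in 2018"; the assumed intervention rate is 70%; "with an alpha of 0.05 and a beta of 0.2 is required"; the result is "a sample size of 163 women per group (total of 326 women"). The recruitment target is 180 per group. Sidedness is not stated.

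**Assumed, because the protocol gives no value.** Share of DPT variance explained by T0 variables, R²: 0.02 to 0.10, with 0.20 as an optimistic bound. Correlation between a T0 score and its follow-up value, r: 0.3 to 0.7. Number of enrolment days: 75 (range 50 to 100) over the stated 3.5 months. Intraclass correlation (ICC) within day: 0.01 to 0.05.

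**1. Reproduce the plan's figure.** With pooled variance, two-sided test and no continuity correction,

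n = [1.960·√(2·0.625·0.375) + 0.842·√(0.55·0.45 + 0.70·0.30)]² / 0.15² = (1.342 + 0.569)² / 0.0225 ≈ 162.3, rounded up to 163.

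This matches exactly, so the sample size was built for the unadjusted test and is not in error. Power at 163 per group is 80.2%.

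**2. DPT uptake with covariate adjustment.** As an approximation, the effective size is 163 / (1 − R²).

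| R² (assumed) | Effective n per group | Power |
|---|---|---|
| 0 | 163 | 80.2% |
| 0.02 | 166.3 | 81.0% |
| 0.05 | 171.6 | 82.1% |
| 0.10 | 181.1 | 84.1% |
| 0.20 | 203.8 | 88.1% |

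**3. Continuous scores with a T0 counterpart.** Adjustment multiplies the variance by 1 − r². The unadjusted test needs 1/(1 − r²) times as many women for equal precision. If it has 80% power, the adjusted analysis has power Φ(2.80/√(1 − r²) − 1.96).

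| r (assumed) | Variance factor | Extra women if unadjusted | Adjusted power |
|---|---|---|---|
| 0.3 | 0.91 | 10% | 84% |
| 0.5 | 0.75 | 33% | 90% |
| 0.7 | 0.51 | 96% | 98% |

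**4. Chance imbalance.** The standard deviation of the between-group difference in a standardised baseline score is √(DE·2/180), where DE = 1 + (m − 1)·ICC and m = 360/75 = 4.8 women per day.

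- ICC 0: 0.105
- ICC 0.01 (DE 1.04): 0.107
- ICC 0.05 (DE 1.19): 0.115

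Day randomisation therefore adds little to chance imbalance. The basic amount still matters: an imbalance of 2 × 0.105 = 0.21 in a score with r = 0.5 shifts the unadjusted follow-up difference by 0.5 × 0.21 = 0.105 standard deviations.

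**5. Clustering is a separate matter.** If the design effect is respected, unadjusted power at 163 per group is 78.7% (ICC 0.01) or 73.0% (ICC 0.05) at 75 days. Across 50 to 100 days it is 77.7% to 79.1% and 68.8% to 75.2% respectively. Steps 2 and 3 do not include this penalty.

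**The case against.** The strongest reply is that nothing here is wrong. Unadjusted tests are valid under randomisation, they agree with the sample size, and covariate lists often sit in a full protocol or analysis plan that is not shown. The first two parts stand as far as bias and consistency go (clustering apart), so this is a matter of efficiency. The third does not dispose of the point: the article states the tests it will use, and a better method using data already planned can replace them.

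Several stronger readings are tempting but not supported:

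- **That the estimate is biased.** Lack of adjustment does not bias it under sound randomisation.
- **That adjusted analysis is forbidden.** "No additional analysis is planned" stands under a heading that gives subgroup analyses as its example, and per-protocol and missing-data sensitivity analyses are planned elsewhere.
- **That T1, T2 and T3 are tested separately.** The article does not say how repeated measures are handled; separate testing is only an inference from the tests named.
- **That T0 holds the full HLS-EU-Q16.** The article mentions T0 health literacy questions but lists that scale only for T1 to T3. A matching baseline score is likely, not confirmed. The same caution applies to a vaccination-attitude item.
- **That baseline significance tests are planned.** The text says characteristics will be compared, without explicitly assigning p-values to that comparison.

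The section on outcome assessment {18a} also says baseline data serve to control unwanted bias. That concerns a datasheet on all invited women and names no adjustment, so it does not answer the point.

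**Conclusion.** The point holds as a worthwhile, inexpensive improvement. The article commits to unadjusted two-group tests and puts none of its T0 data into a stated outcome model.

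For the primary outcome the gain is about 1 to 4 power points at R² of 0.02 to 0.10. A gain of 8 points needs R² of 0.20, which nothing in the protocol supports. The larger gain, 9% to 49% of variance, applies only to continuous secondary scores measured at T0 on the same scale. All these sizes rest on assumed correlations.

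A reader might infer that adjustment also deals with allocation by day. It does not: it reduces the effect of imbalance in measured variables, while within-day correlation needs its own correction and may cost more power than adjustment recovers.

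**What to change.** Amend {20a}, before outcome data are seen, to prespecify:

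1. **DPT uptake:** a risk difference with 95% confidence interval, obtained by standardisation from a regression adjusted for a short fixed list of T0 variables known to be collected, such as age, education and country of origin. Add vaccination attitude if the T0 questionnaire contains it. Cluster the standard errors on enrolment day.
2. **Continuous scores measured at T0 on the same scale:** one baseline-adjusted model over T1 to T3 that also accounts for enrolment day.
3. **Baseline characteristics:** a descriptive comparison, not one used to judge randomisation.

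The cost is mainly analysis wording. No new data are needed for the listed demographic covariates, provided the enrolment date is kept in the data set. The downsides are small: a rule for incomplete T0 covariates, some model dependence, and intervals that may widen once day clustering is respected.
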